### Study timelines

Participant recruitment and data collection will occur from 1 February to 30 May 2026. Data cleaning, verification, and preliminary analysis are planned for June 2026, followed by final statistical analysis and synthesis of results in July 2026. Final results will therefore be available by 31 July 2026.

### Data management

Audio recordings and transcripts will be de-identified using participant codes, and direct identifiers such as names will not be used. Digital files will be stored on password-protected, encrypted computers, and physical documents like consent forms and field notes will be kept in locked cabinets with restricted access. Only the research team will have access to the data. Data used in reporting will be presented in aggregate or with pseudonyms to prevent participant identification. Audio recordings will be securely destroyed after transcription verification, and all data will be retained and disposed of per institutional ethical guidelines. Participants’ time will be compensated in accordance with local ethics regulations, in the form of snacks and refreshments.

### Statistical methods: Sample size and data analysis

The sample sizes for the different phases of the HCD methodology have been described above. However, the exact sample sizes will depend on thematic saturation, a point at which no new information emerges even when additional data are collected. All interviews will be audio-recorded and professionally transcribed verbatim by experienced qualitative researchers. The transcripts will be checked for accuracy by replaying and listening to the audio recordings, and any inconsistencies will be identified and corrected.

The corrected transcripts will be uploaded into NVivo software for thematic analysis using an inductive approach. To minimize subjective bias, two independent analysts (JI and AS) will conduct the analysis. Each analyst will independently and repeatedly read a few of the transcripts to achieve familiarity with the data (data immersion), identify recurring and significant patterns, and develop codes. Through consensus, the analysts will develop an initial codebook based on the independent codes, which will be used to code the remaining transcripts and remain open to newer codes. We will iteratively refine and group the codes into categories and subsequently into themes, and present them alongside illustrative quotes to support interpretation. Reporting of the qualitative findings will adhere to the Standards for Reporting Qualitative Research (SRQR) guidelines [27].

In SUS data analysis, we will normalize the data by subtracting 1 from each odd-numbered question (questions 1, 3, 5, 7, and 9) and 5 from each even-numbered question (questions 2, 4, 6, 8, and 10). This process will create new values, which will be summed to produce a total score, which will be multiplied by 2.5 to yield scores that will range from 0 to 100, with 68 as the average score [26]. We will categorize the SUS scores as ≤50, 51–68, 68–80.3, and more than 80.3 to suggest unacceptable, poor, good, and excellent strategies/prototypes, respectively [28]. Prototypes with SUS scores ≥68 will be considered usable and may be tested in the planned trial.

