### Phase 3: Implementation phase: prototype testing, iteration, and refinement

We will conduct two rounds of prototype testing, low and high fidelity, each involving 12–16 participants deemed sufficient to attain thematic saturation, including people with TB/HIV, TB and HIV focal persons, MoH officials, and pharmacy health workers. In the low-fidelity phase, participants will engage in 60-minute individual interviews with a talk-aloud session to review the prototype, discuss what works, and provide feedback on desirability, feasibility, and viability using a 5-point Likert scale, ranging from a low to high score (1 = Very low, 2 = Low, 3 = Moderate, 4 = High, and 5 = Very high). The participants will also compare 2–3 prototype options and vote for their preferred version. Findings from this phase will guide revisions before the high-fidelity phase, during which usability will additionally be assessed using the System Usability Scale (SUS) using a simple, 10-item standardized questionnaire [26]. Each SUS question will be ranked on a 1–5 scale, with the lowest score indicating a strong disagreement with the prototype and the highest score suggesting otherwise. We will implement the SUS until a higher level of acceptability, defined as a median score of >80.3, is reached [26]. A maximum of three iterative refinement cycles will be conducted to allow systematic improvement of prototypes based on user feedback. Prototypes achieving higher SUS and Likert-scale scores will be prioritized for pilot implementation in a hybrid effectiveness–implementation randomized trial at two public primary healthcare facilities in Kampala, Uganda.

If the predefined SUS threshold of >80.3 is not achieved after the maximum number of iterations, the prototype with the highest median SUS score (provided it meets or exceeds the acceptable usability benchmark of ≥68) and demonstrates consistent improvement across rounds will be selected. Qualitative user feedback and feasibility considerations will additionally inform the final selection to ensure contextual appropriateness. This iterative, user-centered approach ensures systematic refinement and selection of the most acceptable, feasible, and effective intervention prototypes.

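### As written, the SUS scoring rule gives −50 to +50 rather than 0 to 100, so no prototype can reach the 68 or 80.3 cut-offs

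*Protocol article*

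**What the plan says.** Three statements in the protocol article bear on this.

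- **Instrument.** The Phase 3 section says usability is assessed "using a simple, 10-item standardized questionnaire". Responses run from 1 to 5, and the two ends are described in the same way for all items: "with the lowest score indicating a strong disagreement with the prototype and the highest score suggesting otherwise".
- **Scoring.** The section on sample size and data analysis normalises responses by "subtracting 1 from each odd-numbered question (questions 1, 3, 5, 7, and 9) and 5 from each even-numbered question". The new values are summed and "multiplied by 2.5 to yield scores that will range from 0 to 100, with 68 as the average score".
- **Use.** Phase 3 continues SUS testing until the median exceeds 80.3, with at most three refinement cycles. If that target is missed, it falls back on the prototype with the highest median, provided the median is at least 68 and has improved steadily. The data analysis section sets four bands (lowest ≤50, highest above 80.3) and treats a score of 68 or more as the mark of a usable prototype that may go into the trial.

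No other section gives a different formula.

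**The concern.** Subtracting 5 from a response that cannot exceed 5 never gives a positive number. Half the items can then only lower the score or leave it unchanged, which cannot be squared with a scale running from 0 to 100. Every numerical SUS cut-off in the protocol assumes that scale: the target that ends iteration, the fallback floor, the quality bands and the usability criterion for the trial. Scores are needed between refinement cycles, so an error would act during data collection and not only at final analysis.

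The description of the response anchors makes matters worse. If 5 is favourable to the prototype on every item, there is no reason to treat odd and even items differently. The odd/even split makes sense only if respondents rate agreement with each statement and the even-numbered statements are reverse-keyed.

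The Introduction also says the protocol is published so that others can replicate and adapt the method, so a wrong formula may be copied.

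**Working it through.** **Inputs**

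- Ten items, five odd and five even, each answered 1 to 5 (Phase 3 section).
- Odd item: x − 1. Even item as written: x − 5. Multiplier 2.5, stated range 0 to 100 (data analysis section).
- Cut-offs 68 and 80.3 (both sections); lowest band ≤50 (data analysis section).

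**Step 1: try to reproduce the stated range**

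Score as written = 2.5 × [Σ(odd − 1) + Σ(even − 5)].

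- Odd items contribute 5 × 0 = 0 up to 5 × 4 = 20.
- Even items contribute 5 × (−4) = −20 up to 5 × 0 = 0.
- Minimum: 2.5 × (0 − 20) = −50. Maximum: 2.5 × (20 + 0) = 50.

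The stated 0 to 100 is not reproduced.

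**Step 2: compare with the cut-offs**

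- A score of 68 needs a sum of 68 / 2.5 = 27.2.
- A score above 80.3 needs a sum greater than 80.3 / 2.5 = 32.12.
- The largest possible sum is 20.

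No individual score, and hence no median, can reach either cut-off. Every possible score is ≤50. This holds whichever way the items are keyed.

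**Step 3: find a rule that does give 0 to 100**

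- Even items as 5 − x: each contributes 0 to 4, so the total runs from 2.5 × 0 = 0 to 2.5 × (20 + 20) = 100.
- All ten items as x − 1: also 0 to 100.

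The first keeps the odd/even split and the constant 5. The second fits the Phase 3 anchors but makes both the split and the 5 pointless.

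**Step 4: response patterns (all odd items the same, all even items the same)**

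| Odd / even response | As written | Even items as 5 − x | All items as x − 1 |
|---|---|---|---|
| 5 / 1 | 0 | 100 | 50 |
| 4 / 2 | 0 | 75 | 50 |
| 3 / 3 | 0 | 50 | 50 |
| 1 / 5 | 0 | 0 | 50 |
| 5 / 5 | 50 | 50 | 100 |
| 1 / 1 | −50 | 50 | 0 |

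If even items are reverse-keyed, the best (5 / 1), neutral (3 / 3) and worst (1 / 5) respondents all score 0 as written. Favourable answers on the two halves cancel, and the score no longer separates a good prototype from a poor one.

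The 5 / 5 row shows the effect of the anchors. A satisfied participant who has been told that 5 is favourable on every item gets 50 under the 5 − x rule.

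**The case against.** The strongest reply is that this is a slip of operand order with an obvious intent. The stated range shows what was meant, the instrument is standardised and cited, and negative or zero totals on the first few questionnaires would expose the mistake. An analyst with a ready-made scoring script would never meet it. That stands as a statement about likelihood: the unreachable cut-offs follow only if the sentence is applied literally. It does not remove the contradiction, and the text alone leaves two repairs that both give 0 to 100.

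A second reply is that no section says the even items are negatively worded. On the anchors the protocol does give, the literal score still rises with favourability and is simply the all-items-minus-1 score shifted down by 50. That is correct, so the cancelling in Step 4 rests on an inference. The inference is well supported, because nothing else explains the odd/even split. Step 2 does not depend on it.

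A third reply is that the SUS does not decide alone. Likert ratings also count in choosing prototypes, qualitative feedback informs the fallback choice, and the number of cycles is capped. That also stands, and no hypothesis test rests on the SUS. But the 80.3 target and the 68 floor are the only numerical cut-offs stated for stopping and selection, and both fail.

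Finally, the anchor sentence is a brief description and not an interviewer script, so mis-anchoring in the field is a risk and not a known fact.

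**Conclusion.** The concern holds. The stated rule yields −50 to +50 against a stated 0 to 100. Its ceiling of 50 lies 18 points below the lower cut-off (68 − 50) and 30.3 points below the upper one (80.3 − 50). Followed literally, iteration would always run to its cap, no prototype would qualify under the fallback, and all would be classed as unacceptable.

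This conclusion needs only the 1-to-5 response scale and the formula as printed. The further conclusion, that the literal score loses its meaning as a usability measure, assumes reverse-keyed even items.

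It must be corrected because the protocol fixes a wrong operation for a decision rule; this is not a detail left to a later document. The anchor wording is equally urgent for a practical reason: a wrong formula can be repaired from retained item responses, but answers given under wrong anchors cannot.

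**What to change.** 1. **Data analysis section.** Replace the normalisation sentence with: subtract 1 from the response to each odd-numbered item; subtract the response to each even-numbered item from 5; sum the ten values and multiply by 2.5. The range of 0 to 100 and the cut-offs can then stay as they are.
2. **Phase 3 section.** Define the anchors as agreement with each statement (1 = strongly disagree with the statement, 5 = strongly agree with the statement), and note that the even-numbered statements are reverse-keyed.
3. **Before the high-fidelity round.** Confirm the item wording and keying against the cited questionnaire, check that the printed anchors and the interviewer explanation match, and test the scoring script on known patterns: 5 / 1 must give 100, 3 / 3 must give 50 and 1 / 5 must give 0. Keep the raw item responses so that scores can be recomputed.

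The cost is two reworded sentences and a short check of the script and the form. Sample size and timelines are unaffected.

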### Ethics statement

We obtained administrative clearance from the Directorate of Public and Environmental Health, Kampala Capital City Authority (Ref: DPHE/KCCA/1301/01). Ethical approval was obtained from the Makerere University Infectious Diseases Institute Research Ethics Committee (Ref: IDI-REC-2024–98) and the Uganda National Council for Science and Technology (Ref: HS4397ES). Participants will provide informed consent in writing or thumbprint after receiving comprehensive information about the study process, rationale, purpose, potential risks and benefits, and ethics approvals. We will also explain existing measures to protect the privacy and the confidentiality of participant information, including the right to withdraw from the study and compensation for the time spent in the study. All qualitative data will be de-identified and stored on a password-protected, encrypted laptop, with physical documents kept in locked cabinets. Only the research team will have access. Audio recordings will be destroyed after transcription verification, and data will be retained and disposed of following institutional ethical guidelines.

The study will be conducted in accordance with the principles of the Declaration of Helsinki on ethical conduct of research involving human participants.

### Dissemination plan

Study findings will be shared at multiple levels to ensure uptake and impact. At the health facility level, results will be communicated to health workers and people with TB/HIV through validation meetings and health education talks. At the district and national level, synthesized reports and presentations will be shared with the Directorate of Public and Environmental Health, Kampala Capital City Authority (KCCA), the Ministry of Health, and the National TB and Leprosy Control Program (NTLP) to inform policy and program implementation. At the international level, the broader scientific community will be reached through conference abstract presentations and peer-reviewed manuscript publications.

### Patient and public involvement

Patients and community members were not involved in the development of this protocol. Also, no patient and public involvement activities were conducted.

## Discussion

Our study will use the HCD methodology to adapt person-centered strategies for integrating TB treatment into community pharmacies among people with TB/HIV in Kampala, Uganda. The main goal is to develop and adapt implementation strategies that are stakeholder-designed, contextually grounded, feasible, and acceptable. We will follow the steps of the HCD methodology, drawing on barriers and facilitators identified in a qualitative study that employed the consolidated framework for implementation research (CFIR) tool. The CFIR domains will inform the inspiration phase of the HCD methodology by providing a structured framework to interpret qualitative findings. Specifically, CFIR constructs identified from interviews and observations will be mapped to insights, which will then guide the formulation of *“How Might We”* (HMW) questions. These HMW questions will be translated into design opportunities, which will subsequently be used to develop actionable prototypes. This approach ensures that the HCD process is theoretically grounded in implementation science and that each phase systematically builds on CFIR-informed qualitative data.

The rationale for using community pharmacies for delivering TB treatment is based on their potential to deliver person-centered care and improve health system efficiency. Studies have shown that ART integration into community pharmacies for people with HIV reduces the healthcare provider workload [11] and frees up their time to care for individuals who require critical care [29,30]. At the health system level, the approach has led to decongesting health facilities [30]. Therefore, the integration of TB treatment into community pharmacies has several untapped potential. Community pharmacies offer greater convenience by enabling people with TB/HIV to refill both TB and HIV medications at a single location and time, hence reducing both direct and indirect costs associated with treatment access [31]. This flexibility may reduce the risk of unintended TB/HIV status disclosure [32] and mitigate both self and community stigma associated with TB and HIV [11,30,33–35].

Evidence also shows that in urban settings, people with TB/HIV often have unstable or changing physical addresses [34], and community pharmacies offer a more efficient and adaptable service delivery approach when compared with other community-level differentiated service delivery models. Our proposed integration of TB treatment into community pharmacies thus aims to extend these benefits recorded among people with HIV to those with TB/HIV.

In our planned pilot, individually randomized, hybrid type 2 effectiveness-implementation trial, we will primarily assess the effectiveness of integrating TB treatment into community pharmacies. Effectiveness outcomes will include HIV viral load suppression and TB treatment success at six months. Also, we will evaluate key implementation outcomes, including feasibility, acceptability, and fidelity as secondary outcomes. We aim to generate robust evidence to inform and strengthen the efforts of the national TB program in Uganda and similar settings in advancing person-centered care for people with TB/HIV, including contributing to ending the TB epidemic by 2035.

### Study strengths and limitations

A key strength of the study is the planned use of HCD methodology, which emphasizes empathy and direct engagement with participants at various health systems levels: people with TB/HIV at the community level, TB and HIV focal persons and community pharmacy healthcare providers at the health facility level, and MoH officials at the national level. The use of HCD methodology facilitates the identification of context-specific needs, preferences, and challenges that may be overlooked via conventional or researcher-driven methods.

By grounding implementation strategies in the lived experiences of participants or real-world settings, the methodology may enhance the relevance, feasibility, and acceptability of the intervention and its strategies. Besides, the methodology emphasizes co-design and promotes early and active participant engagement to foster ownership and increase strategy adoption and sustained use. The iterative nature of the methodology, through activities such as prototyping and real-time feedback, supports the development of strategies that are responsive and adaptable to the local contexts. Lastly, the methodology inherently amplifies the voices of marginalized or underrepresented groups, thereby contributing to more equitable implementation strategies.

Despite the strengths of HCD methodology, there are certain limitations. The methodology can be time- and resource-intensive, requiring skilled facilitation and multiple engagement rounds, which may be challenging. To mitigate this limitation, we will use experienced and skilled individuals with expertise and training in the methodology. Additionally, most HCD-generated solutions/prototypes are often context-specific and may limit generalizability. There is also the risk of incomplete representation of participant engagement, although our proposed multi-level participant engagement approach will likely mitigate this limitation. In addition to subjective bias during data analysis, the HCD process may be affected by selection bias, as participants attending workshops may differ from those who do not; social desirability bias, where participants provide responses they perceive as favorable; and facilitation or group influence bias, where dominant voices may shape group decisions. To minimize these biases, we will use purposive and consecutive sampling, conduct confidential and independent voting, and employ trained facilitators to ensure equitable participation and capture diverse perspectives. Finally, the methodology is effective at generating user-centered solutions but may not fully address structural or system-level barriers. To mitigate this limitation, we will combine the HCD methodology with CFIR to ensure both user-centeredness and methodological rigor, while enhancing the potential for scalability and sustainability of resulting implementation strategies.

## Conclusion and recommendation

Our proposed HCD methodology will adapt person-centered implementation strategies that are contextually relevant, practical, feasible, and acceptable to all participants. The strategies will inform the integration of TB treatment into community pharmacies in a future pilot randomized trial targeting people with TB/HIV in Kampala, Uganda.

This methodology may be useful in other contexts where integration of services is becoming recommended as global health resources become increasingly limited.
